### 10.1.3 Solicited AEs

Diary cards will collect the timing and severity of predefined Solicited AEs listed in [Appendix B](#). Solicited local AEs and solicited systemic AEs collected for 7 days (Day 0 to Day 6 for COV005 while Day 0 to Day 7 for rest of studies) after vaccination for each dose will be summarized respectively. The strategy for pooling the data across different studies is provided in [Appendix B](#).

Each solicited AE will be summarized by treatment group at the following time intervals: Days 0-7, and Days 0 to day 7 individually (for PA only). Each time interval will be repeated for after dose 1, after dose 2 and after any dose. For each time interval, the count and percentage of participants will be determined for each of the following categories: participants evaluated, participants with any event, mild events, moderate events, severe events, and potentially life-threatening events. Participants should not be double counted; therefore, the event of greatest severity will be used for participants with more than one episode of the same event. Similar counts and percentages will be presented for solicited local AEs “Overall” and solicited systemic AEs “Overall”. For participants evaluated for diary cards, missing values will be treated as missing in the calculation.

A listing of all solicited AEs will be provided at the time of the primary analysis.

### 10.1.4 Unsolicited AEs

All AEs are unsolicited AEs unless categorized as solicited AEs. Unsolicited AEs from the start of each dose through 28 days (ie, day of vaccination and the following 27 days) will be summarized. Summaries will be produced of:

- Number of participants with unsolicited AEs by treatment group, system organ class and preferred term
- Number of participants with unsolicited AEs, assessed by investigator as possibly related to investigational product, by treatment, system organ class and preferred term
- Number of participants with unsolicited AEs  $\geq x\%$  in either treatment group, by treatment and preferred term where x may be 1, 3 or 5

In the summary of number of participants, should a subject experience multiple events within a SOC or PT, the subject will be counted only once for that SOC or PT.

A listing of all unsolicited AEs will be provided at the primary analysis.

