### **10.1 Adverse Events**

#### **10.1.1 Reporting of Adverse events**

All local and systemic AEs that occur within 28 days after each vaccination observed by the Investigator or reported by the participant, will be recorded by the participants in the Diary of Symptoms and by the Investigators in the study CRF. For COV001, diary cards for the second vaccines will not be filled out for participants in groups 2f, 2g, 4c and 4d. For COV002, solicited and unsolicited AEs will be reported for 7 days only for group 1-3, 5, 7, 8, 11 and 12 and a subset of up to 3000 participants for groups 4, 6, 9, and 10. In COV003, solicited AEs will be reported for a subset of 200 participants.

SAEs and Adverse Events of Special Interest will be collected throughout the study period.

Adverse events will be coded using the Medical Dictionary for Regulatory Activities (MedDRA) Version 23 or higher.

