### **B 3 Solicited Adverse Events**

Solicited AEs as defined in the CSP and in the patient diaries are presented in [Table B2](#) below. Studies COV001 and COV002 have identical terms in the CSPs and patients diaries. Study COV003 terms are synonymous with the terms in Studies COV001 and COV002. Study COV005 has identical or synonymous terms for 12 of the solicited AEs, but some protocol-specified events are not collected in the patient diary (ie, pain, warmth, malaise, nausea, vomiting) and an additional local event, bruising, is collected in the patient diary.

| Table B2 CSP-specified Solicited Adverse Events and Patient Diary Terms for these Events by Study |                                 |                                     |                                 |                            |                  |                        |
|----------------------------------------------------------------------------------------------------------|---------------------------------|-------------------------------------|---------------------------------|----------------------------|------------------|------------------------|
| Adverse Event                                                                                     | CSP Terms                |                                     |                                 | Patient Diary Terms |                  |                        |
| Study                                                                                             | COV001, COV002           | COV003                       | COV005                   | COV001, COV002      | COV003    | COV005          |
| Pain                                                                                                     | Pain/
Pain at injection site | Pain/
Injection site pain        | Pain/
Pain at injection site | Pain                       | Pain             | -                      |
| Tenderness                                                                                               | Tenderness                      | Sensitivity                         | Tenderness                      | Tenderness                 | Sensitivity      | Tenderness             |

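### The residual definition of unsolicited AEs lets first-week reactions from participants without solicited reporting, mainly about 9800 in COV003, mix with other AEs in the pooled unsolicited tables

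*SAP*

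**What the plan says.** Four parts of the SAP bear on this.

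- **The category.** Section 10.1.4: "All AEs are unsolicited AEs unless categorized as solicited AEs". The window follows: "Unsolicited AEs from the start of each dose through 28 days (ie, day of vaccination and the following 27 days) will be summarized".
- **How solicited AEs arise.** Section 10.1.3: "Diary cards will collect the timing and severity of predefined Solicited AEs listed in" Appendix B. They are summarised over Days 0-7 (Days 0-6 collected in COV005).
- **Who has solicited reporting.** Section 10.1.1: "In COV003, solicited AEs will be reported for a subset of 200 participants". For COV001, "diary cards for the second vaccines will not be filled out for participants in groups 2f, 2g, 4c and 4d". For COV002 the restriction covers both kinds of event: "For COV002, solicited and unsolicited AEs will be reported for 7 days only for group 1-3, 5, 7, 8, 11 and 12", plus "a subset of up to 3000 participants for groups 4, 6, 9, and 10".
- **What the COV005 diary omits.** Appendix B 3: "some protocol-specified events are not collected in the patient diary (ie, pain, warmth, malaise, nausea, vomiting".

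Section 10.1.1 also has all local and systemic AEs in the 28 days after each dose recorded by investigators in the CRF. For COV003 it limits only solicited AEs. Section 10.1.4 plans summaries by system organ class and preferred term, a summary of possibly related events, and one of events at or above a percentage threshold. Sections 7.2 and 10.3 call for the incidence of unsolicited AEs by subgroup, including country.

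**The concern.** The unsolicited tables are where a reader looks for events beyond the expected reactions to an injection. A residual definition serves that purpose only if the expected reactions are captured elsewhere for everyone. Here they are not. A participant without a diary can still report injection site pain, chills or fever to the investigator on Day 1, and that report goes into the CRF. No rule in 10.1.4 says what happens to a term on the Appendix B list that arrives this way.

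Two consequences follow. First, one preferred term can be solicited in one study and unsolicited in another within a single pooled analysis, so the unsolicited, possibly related and threshold tables become a mixed category. Section 1.2 names site pain, tenderness, chills, fever, headache, malaise and myalgia as the most common solicited AEs, so these are the terms most likely to cross over. Second, Brazil is almost entirely without solicited reporting. A comparison of unsolicited AE incidence between countries therefore partly compares diary with no diary.

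**Working it through.** The SAP gives no figure on this point, so there is none to reproduce.

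**1. Which rule decides the category?** Section 10.1.3 speaks of a predefined list, which could mean that the term decides. The SAP's usage elsewhere points to diary capture. Section 10.1.1 confines solicited AEs in COV003 to 200 people, which would make little sense if any matching term in the CRF counted. Table B8 marks pain, warmth, malaise, nausea and vomiting as having no data from COV005, although a term rule would admit CRF reports of them.

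**2. Participants without solicited reporting in COV003.** Planned enrolment is 10 000 (Table 1): 1 - 200/10 000 = 98%, or 9800 people.

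**3. Share of the pool.** Planned total: 1122 + 12 390 + 10 000 + 2070 = 25 582. Let X be the COV002 non-efficacy groups. Table A2 (~19 800, any dose, safety) minus Table A1 (~19 200, any dose, efficacy) gives 600; both are floored to 100, so X is about 500-700.

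- With a diary: 1122 + 3000 + X + 200 + 2070 = 6892 to 7092, or 27-28% of 25 582.
- Reporting unsolicited AEs, if the COV002 sentence is taken literally: 1122 + 3000 + X + 10 000 + 2070 = 16 692 to 16 892.
- The 9800 are 9800/25 582 = 38% of planned enrolment and 58-59% of those reporting unsolicited AEs.
- If COV002 participants outside the named groups and subset did report unsolicited AEs, participants without a diary would number 25 582 - 7092 = 18 490 to 25 582 - 6892 = 18 690, or 72-73% of planned enrolment.

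These mix planned numbers with August 2020 counts and are approximate.

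**4. Possible size within COV003.** All rates here are assumed, as is 1:1 allocation. Let b = 10% be the background unsolicited rate in both arms, p the share with a reaction, and r the share of those reactions recorded spontaneously.

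Share with any unsolicited AE = 0.98 × [1 - (1 - b)(1 - r·p)] + 0.02 × b

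Arm difference = 0.98 × 0.90 × r × (p_vaccine - p_control) = 0.882 × r × (p_vaccine - p_control)

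| Reaction rate, vaccine/control | r = 0 | r = 5% | r = 20% | r = 50% |
|---|---|---|---|---|
| 80/60 or 60/40 | 0 | 0.9 | 3.5 | 8.8 |
| 70/40 | 0 | 1.3 | 5.3 | 13.2 |
| 50/50 | 0 | 0 | 0 | 0 |

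(percentage points)

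**5. Diluted over the pool.** If only COV003 contributes, replace 0.98 by 9800/16 792 = 0.584 (X = 600). The multiplier becomes 0.90 × 0.584 = 0.526. The difference is then 0.5-0.8 points at r = 5%, 2.1-3.2 at 20% and 5.3-7.9 at 50%, for reaction differences of 20-30 points.

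**6. Under a term-and-window rule.** If every Appendix B term with onset in the solicited window were classed by term whatever its source, nothing would enter by this route and the added difference would be 0.

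**The case against.** The strongest reply is that the solicited terms are predefined, so categorisation could follow the term and nothing would cross over. That reading is available, but COV003's 200-person limit and the COV005 entries in Table B8 sit badly with it. An open choice between two readings would itself let two programmers produce different tables.

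Several stronger inferences are tempting, and the SAP does not support them.

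- **A false vaccine excess.** The studies are described as randomised and blinded, and nothing ties diary status to arm. An arm difference from these events is a genuine difference in reactions, and it is zero if the arms react equally. COV003 controls received MenACWY at dose 1, which may itself cause reactions, and saline at dose 2.
- **Most of the pool affected.** Most planned participants have no diary, but Section 10.1.1 read literally removes the COV002 participants outside the named groups and subset from unsolicited reporting too.
- **All reactions affected in COV005.** Its diary does collect tenderness, temperature, feverishness, rigors, headache, and muscle and joint pain. Only the five omitted items are exposed.
- **Masking of a signal.** Tables by preferred term show injection site pain or pyrexia by name, so these do not hide another term.

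It is also fair to object to removing such events from the main table, because some early headaches and fevers are unrelated to vaccination and are legitimate spontaneous reports. The fix below keeps them in.

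**Conclusion.** The point stands as a classification defect. The residual rule combined with partial solicited reporting yields an unsolicited category whose content depends on whether a participant had a diary. The main route is the 9800 planned COV003 participants. Dose 2 in COV001 groups 2f, 2g, 4c and 4d and the five COV005 items add to it by an amount the SAP does not let one calculate.

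The effect on the tables cannot be fixed from the document. The ranges above rest wholly on assumed reaction, background and spontaneous-reporting rates, with zero as the lower end. Confounding of country with diary status follows from the design without assumed rates; its effect on the tables still requires that some reactions be recorded outside the diary. It affects comparisons between countries, not the randomised comparison within one. Actual enrolment may shift the shares.

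**What to change.** In Section 10.1.4, flag every AE that codes to a Table B2 term, has onset on Day 0-7 after a dose (Day 0-6 in COV005), and was not collected by diary for that participant and dose. Then:

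- keep flagged events in the overall unsolicited table;
- present the unsolicited, possibly related and threshold tables also without flagged events;
- split those tables by diary status (yes/no);
- show flagged events in a table of their own.

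The cost is a paragraph of SAP text, a preferred-term mapping from Table B2 and a few extra tables. Some early headaches or fevers unrelated to vaccination will carry the flag, but they stay visible in the overall table. No new data collection is needed.

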| All participants analysis set | All participants screened for the studies, to be used for reporting disposition and screening failures.                                                                                                                                                                                                                                                                                                                                                                                                                                                                                                |
| Any Dose for Safety           | All randomized adult participants who received at least 1 dose of study intervention (AZD1222 or control).
Participants who withdraw consent or assent to participate in the study will be included up to the date of their study termination.
Erroneously-treated participants (eg, those randomized to treatment A but are actually given treatment B) are accounted for in this analysis set by assigning them to the treatment they actually received. A participant who received at least one dose of AZD1222 is classified as AZD1222. This analysis set will be used for safety analysis. |
| Any Dose for Efficacy         | All participants in Any Dose for Safety but for groups in COV002, only efficacy groups (ie, groups 4, 6, 9,10) will be considered.
This analysis set will be used for efficacy analysis.                                                                                                                                                                                                                                                                                                                                                                                                            |
| Dose1 SD for Safety           | Only participants who received SD as the first dose of AZD1222 or in corresponding control group in Any Dose for Safety. The treatment assignment will follow the same rule of Any Dose for Safety analysis set. This analysis set will be used for safety analysis.                                                                                                                                                                                                                                                                                                                                   |

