## **10. SAFETY ANALYSIS**

Safety summaries described below will be performed by treatment group (AZD1222 and Control) for analysis sets planned in [Table A2](#).

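### Unsolicited AEs are summarised over 28 days with no collection-based denominator, although COV002 reporting is limited to 7 days in listed participants, so pooled absolute rates can be understated.

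*SAP*

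**What the plan says.** **Window.** Section 10.1.4: "Unsolicited AEs from the start of each dose through 28 days (ie, day of vaccination and the following 27 days) will be summarized". It asks for participant counts by system organ class and preferred term, overall and for related events. It also asks for a table of terms that reach x% "in either treatment group, by treatment and preferred term where x may be 1, 3 or 5".

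**Analysis set.** Section 10: "Safety summaries described below will be performed by treatment group (AZD1222 and Control) for analysis sets planned in" Table A2. That table lists unsolicited AEs as an endpoint for the any-dose set (about 19,800) and for the set whose first dose was SD (about 16,000). Table 3 in section 5 defines the any-dose safety set as "All randomized adult participants who received at least 1 dose of study intervention (AZD1222 or control"). Neither set requires that unsolicited AEs were collected.

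**Collection.** Section 10.1.1 opens with a general rule for recording: "All local and systemic AEs that occur within 28 days after each vaccination observed by the Investigator or reported by the participant". It then says: "For COV002, solicited and unsolicited AEs will be reported for 7 days only for group 1-3, 5, 7, 8, 11 and 12", and extends this to "a subset of up to 3000 participants for groups 4, 6, 9, and 10". The following sentence restricts COV003 as well, but for solicited events alone: "In COV003, solicited AEs will be reported for a subset of 200 participants".

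**Denominator.** Section 10.1.3 gives solicited AEs a category for participants evaluated. Section 10.1.4 has no counterpart.

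**The concern.** The analysis window is 28 days for everyone in the safety set. For part of COV002, the collection rule names unsolicited AEs and stops at 7 days. For the remaining participants of groups 4, 6, 9 and 10 the text does not say whether unsolicited AEs are collected at all. A programmer who follows 10.1.4 and Table A2 literally divides by the whole set. A participant who could not contribute an event on days 8 to 27, or on any day, then counts as having had none.

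Three outputs are exposed:

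- The pooled absolute frequencies, in a plan written to support a marketing application.
- The x% table, because a term can miss the cut-off through dilution alone.
- Incidence of unsolicited AEs by country, which sections 7.2 and 10.3 require. All of the affected collection is in the UK, so the UK could look safer than Brazil or South Africa only because fewer participants were asked, or were asked for a shorter time.

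**Working it through.** **Plan's own figure.** Day of vaccination plus the following 27 days is 1 + 27 = 28 days. The window is internally consistent; the mismatch is with collection.

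**Inputs from the SAP**

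- Any-dose safety set: about 19,800 (Table A2). Any-dose efficacy set: about 19,200 (Table A1). The efficacy set is the safety set without the COV002 non-efficacy groups.
- COV002 non-efficacy adults in the safety set: 19,800 − 19,200 = about 600 (501 to 699, because both counts are floored to 100).
- COV002 participants under the 7-day rule: at most 600 + 3,000 = 3,600.
- Planned enrolment (Table 1): 1,122 + 12,390 + 10,000 + 2,070 = 25,582. The three studies other than COV002 sum to 13,192.

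**Assumed, because the SAP does not give them**

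- Number of COV002 participants in the 19,800, called C: 6,608 (19,800 − 13,192, the other studies at full plan), 9,590 (19,800 × 12,390/25,582, proportional to plan) or 12,390 (COV002 at full plan).
- f, the share of participants with an event within 28 days who already have one by day 7: from 0.25 (7/28, uniform onset) to 1.
- Equal true rates across studies, and a COV002 subset filled to 3,000.

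**Three readings of the COV002 sentence**

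- A: the rest of COV002 reports no unsolicited AEs. Displayed/true = (19,800 − C + 3,600f)/19,800.
- B: the rest follows the 28-day rule. Displayed/true = (19,800 − 3,600 + 3,600f)/19,800.
- C: the limit concerns diary reporting only, and investigators record events for 28 days. Displayed/true = 1.

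Example for A with C = 9,590 and f = 0.25: (10,210 + 900)/19,800 = 0.561. For B with f = 0.25: (16,200 + 900)/19,800 = 0.864.

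| COV002 in set (C) | No collection under A | A: f = 0.25 | A: f = 1 | B: f = 0.25 | B: f = 1 |
|---|---|---|---|---|---|
| 6,608 | 3,008 (15%) | 0.71 | 0.85 | 0.86 | 1.00 |
| 9,590 | 5,990 (30%) | 0.56 | 0.70 | 0.86 | 1.00 |
| 12,390 | 8,790 (44%) | 0.42 | 0.56 | 0.86 | 1.00 |

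**Effect on the 1% cut-off.** The true rate needed to display 1% is 1% divided by the ratio. Under A with C = 9,590 this is 1/0.697 = 1.4% to 1/0.561 = 1.8%.

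**Effect by country (illustration).** Take COV001 and COV002 proportional to plan: 19,800 × 1,122/25,582 = 868, plus 9,590, gives 10,458 UK participants.

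- A: (868 + 900)/10,458 = 0.17 to (868 + 3,600)/10,458 = 0.43.
- B: (10,458 − 2,700)/10,458 = 0.74 to 1.00.
- The COV002 limit does not touch Brazil or South Africa, so their ratio stays at 1.

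**The case against.** The best defence is that the COV002 sentence is ambiguous. Section 10.1.1 opens with a 28-day rule that covers both participant diaries and investigator records in the CRF. The sentence just before the COV002 restriction is about diary cards, so a diary-only meaning cannot be excluded, and under it nothing is diluted. This stands, and it is why the size is given by reading. It does not remove the conflict: the restriction names unsolicited AEs without mentioning diaries, whereas the COV003 sentence names solicited AEs only.

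A second defence is that 10.1.4 speaks of numbers of participants, so only the x% item strictly needs a percentage. That also stands. The whole-set denominator is implied by section 10, Table 3 and Table A2 and is not written in 10.1.4. The accurate statement is that no collection-based denominator is set.

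Third, the harm has limits:

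- If collection does not depend on arm, both arms are diluted alike and ratios between them are roughly kept.
- SAEs and AESIs are collected throughout the study.
- The other 10.1.4 tables have no cut-off, and a full listing is planned, so no term disappears from the report.

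A reader might infer that about a third of participants certainly have no capture and that rates are certainly cut to between a half and two thirds. The SAP does not support this. It needs reading A, and it comes from using planned enrolment of 25,582 as the base. That total includes people whom section 5 excludes, such as children and COV002 groups 11 and 12.

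**Conclusion.** The point holds as a mismatch between collection and analysis that can understate absolute rates; it does not show that the rates will be understated. On the any-dose safety set of about 19,800, the displayed 28-day rate is about 42-85% of the true rate under reading A, about 86-100% under reading B, and undiluted under reading C. Any bias is downward.

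These ranges rest on the assumed COV002 share, the assumed f, equal true rates across studies and a subset filled to 3,000. A smaller subset would lower the ratio under A and raise it under B. The planned totals behind the assumed shares include some excluded groups, so the limits are approximate. Which reading is right cannot be settled from the SAP.

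Absolute rates, risk differences, the x% table and by-country incidence are exposed. A reader might also infer a biased comparison between vaccine and control, or lost safety signals. The documents support neither: nothing in them ties collection to arm, and serious and special-interest events fall outside the restriction.

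**What to change.** 1. In 10.1.1, reconcile the 28-day and 7-day statements with 10.1.4. Say whether the COV002 limit covers all unsolicited reporting or diaries only, and what applies to the rest of groups 4, 6, 9 and 10.
2. Add a flag that records, for each participant, whether unsolicited AEs were collected and for how long.
3. In 10.1.4, make the flagged participants the denominator. Limit the 28-day table to those with 28-day collection, and add a separate Day 0-7 table that includes any participants with 7-day collection only.
4. Apply the 1/3/5% cut-offs and the by-country summaries to those rates.

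If the diary-only meaning is confirmed, step 1 is enough and COV002 stays in the 28-day table.

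The cost is one flag, a changed denominator, a smaller N and somewhat higher reported rates. Under reading A with C = 9,590, the 28-day table would rest on about 10,200 participants (7,410 to 13,192 over the assumed sizes). The Day 0-7 table would rest on about 10,210 + 3,600 = 13,810 (11,010 to 16,792).
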